### Interventions

Patients are scheduled for a minimum of 10 and a maximum of 20 treatment sessions, distributed as one/two sessions each weekday. Each session consists of 30 min of neuromodulation (rTMS or tDCS) coupled with 60 min of intensive motor or language training. The decision on whether to provide rTMS or tDCS is individualized based on specific patient and lesion characteristics.

Notably, the coupling between neuromodulation and task training represents a therapeutic application of the concept of metaplasticity. In fact, metaplasticity has been defined as any change in the direction or degree of synaptic plasticity based on prior neural activity (59). A typical study design investigating metaplasticity applies multiple rTMS sessions within the same day (accelerated rTMS), with minutes/hours between sessions (60). Compared to single rTMS, it has been demonstrated that accelerated rTMS may produce additive strengthening of neuroplastic changes, both for excitatory (60) and inhibitory (61) paradigms. Another way of exploiting the therapeutic potential of metaplasticity is through the combination of rTMS with task training. Previous systematic reviews and randomized controlled trials have already demonstrated the beneficial effect of rTMS delivered before therapy for aphasia, lower limb, and upper limb motor function in stroke patients (62–64). In this perspective, for the present study, neuromodulation is the metaplastic ‘primer' setting the direction and degree for subsequent neuroplastic changes promoted by intensive task training.

#### Neuromodulation – Navigated rTMS

rTMS is applied with the following parameters: waveform: monophasic; intensity: 90% resting motor threshold (RMT); pulse frequency: 1 Hertz; total number of pulses: 1800. The choice of the target is determined based on anatomical considerations and results from neurophysiological and neuroimaging assessments; hence, the area of highest activity among those structures anatomically located near the tumor is considered the target. For instance, by performing motor and language mapping, we could identify active targets at the level of targeted areas, such as the hand knob or sites where speech arrest was detected. We also consider the center of mass of fMRI mapping related to hand movement and speech production as potential hotspots for neuromodulation.

#### Neuromodulation – tDCS

In those cases of subcortical tumors potentially affecting a wider area and more than one function, tDCS is performed with the aim of inhibiting (cathodal stimulation) distributed areas related to functions potentially at risk of being compromised, while at the same time promoting the activation (anodal stimulation) of safer areas within the same functional network.

#### Training of functions at risk of being compromised

Training is performed immediately after inducing a virtual lesion, focusing on functions related to structures targeted by neuromodulation. Motor, language, and/or cognitive functions are selected at the beginning of the protocol, considering the anatomical location of the tumor, medical condition, and pattern of activation by each of the assessed functions in the fMRI.

Detailed design and monitoring of training sessions are gathered, including goals pursued in any session, assigned activity, number of repetitions, and performance.

##### Prehabilitation motor training

Patients undertake intensive motor training sessions soon after (TMS) or during (tDCS) neuromodulation, i.e., in the condition of a virtual brain lesion (targeted area temporarily inhibited). This way, the brain must recruit alternative resources, which cumulatively determine neuroplastic changes and a stable shift of functional activation patterns away from critical areas.

There is a potentially infinite range of activities that could be trained; to be systematic, we defined a taxonomy of exercises based on anatomical and functional domains. Considering, for instance, the upper limb, we decided to prioritize tasks based on proximal (reaching and hand orientation) or distal (finger individuation and manipulation) components of upper limb movements. Within each component, we consider the integration between upper limb motor function and other body segments and/or task domains. For instance, some tasks may be accomplished by using one arm or hand (unimanual), while others may require the cooperation of both limbs (bimanual coordination) or additional balance and/or cognitive challenges (sequence learning, motor memory, and dual task). The goal is to cover all aspects of upper limb functionality and possibly to promote network connectivity of cortical–subcortical–cerebellar structures related to motor control and executive function, beyond the predominant activation of motor–premotor areas of the affected side (65–68).

Other important concepts of motor learning that we consider are task difficulty, task intensity, and task variability (69). Task difficulty refers to the type of challenge that we impose; for instance, speed, accuracy, the ability to isolate or integrate different motor, and/or cognitive tasks. Task intensity refers to the necessity of a high number of repetitions to promote neuroplastic changes associated with motor learning. Task variability is necessary to avoid patient boredom and generalize the benefits of the training; in fact, training always on the same task makes you proficient specifically on that task, while varying training conditions foster retention and generalization of learning to new tasks (70).

Finally, we should point out that most patients are relatively young adults with limited to no symptoms of motor/cognitive impairments before surgery. Therefore, we consider challenging activities that resemble sports and playful games, such as hitting targets, playing ball games, playing the Piano, and manipulating objects. Two common elements of all interventions are (1) that task performance is made up of discrete repetitions and (2) that outcomes are quantitatively measurable. For instance, preparing a meal, dressing, or tidying the table are motor tasks that cannot be easily divided into repetitions or whose outcome is quantitatively defined. By contrast, hitting targets or playing the piano are made of discrete individual repetitions, require specific spatial and temporal accuracy, the success/error rate can be easily measured, and progression can be monitored over time. To summarize, we prioritize goal-oriented, challenging tasks for their positive impact on neuroplasticity (network activation and connectivity), motor learning (difficulty, intensity, and variability), and motivation (constant monitoring of performance).

Virtual reality is also used to promote the activation of non-canonical pathways related to function (71). Any user can effectively distinguish immersive virtual reality from the real world, evidencing different enough recruited networks. However, training in a virtual environment transfers to real-environment learning (72, 73). This well-documented phenomenon enables virtual reality training to promote the recruitment of alternative pathways in the context of preferential ones.

##### Prehabilitation language and cognitive training

Similar to motor training, sessions are performed soon after TMS or during concomitant tDCS. Patients undertake computerized cognitive training sessions on the online rehabilitation platform “Guttmann NeuroPersonalTrainer”^®^ (GNPT) (74), with a duration of ~60 min per session. Tasks aim at language training (60% of the tasks) and other cognitive functions (40%), consisting of a set of personalized cognitive exercises based on the initial neuropsychological assessment that allows for establishing the profile of cognitive impairment. These tasks are adequately parameterized. To this end, neuropsychologists may define a set of input parameters for every task, such as presentation speed, latency time, or number of images, allowing personalization based on different difficulty levels. Regarding language, tasks are planned and supervised in a personalized way by a neuropsychologist, readjusting their planning if necessary.

Language tasks are oriented to naming and generating words, although other tasks oriented to language expression (grammar, semantics, and writing) and language comprehension (reading, comprehension of words, sentences, texts, and listening) could be contemplated.

For the rest of the cognitive functions, GNPT platform allows programming the following functions: (1) temporospatial orientation; (2) attention (selective, sustained, and divided); (3) memory (visual, verbal, and working memory); (4) executive functions (planning, inhibition, flexibility, sequencing, and categorization); (5) visual gnosis; (6) mental calculation; and (7) constructive praxis.

Furthermore, cognitive training is complemented by the telerehabilitation platform of the Barcelona Brain Health Initiative (BBHI) (75).

Finally, we apply specific tasks to train bilingualism. The objective is to achieve the disturbance of linguistic tasks through the temporary inhibition of the critical areas near the lesion (peritumoral), so that the brain can find alternative resources and facilitate neuroplasticity processes. This linguistic disturbance is made according to the representation of the tumor area (areas of higher functional compromise), to later realize language tasks, such as naming, comprehension, and fluency tasks in two languages (Spanish/Catalan), to enhance residual activities and promote a reorganization of functions during the disturbance. Prior to these procedures, a bilingualism questionnaire is administered to assess the dominant language of each participant.

### Discontinuation, adherence, permission for concomitant care, ancillary, and post-trial care

Intervention is discontinued at the participant's request or in case of adverse events attributable to neuromodulation (seizure). Adherence to treatment is monitored by recording the rate of sessions attended over the total number of planned sessions.

Patients are allowed to undertake any concomitant care during the intervention if it does not interfere with the schedule of the prehabilitation program. However, we also recommend patients avoid other neuromodulation or motor skill training approaches, as they may be counterproductive to the desired outcome of the intervention. For instance, undertaking additional upper limb training sessions outside the prehabilitation protocol may reinforce the activation of peritumoral areas, as the inhibitory effect of neuromodulation might not be present anymore.

In case of post-surgery cognitive and/or neurological deficits, neurorehabilitation (usually 10 to 30 sessions) will be provided by the Guttmann Institute as a service offered to patients who have participated in the research study.

### Dissemination

A summarized version of the study protocol has been published online with ClinicalTrials.gov Identifier NCT05844605 (more information of the SPIRIT WHO trial registration data set are reported in Table 1).

**Table 1 T1:** SPIRIT WHO trial registration data set.

**Data category**	**Information**
Primary registry and trial identifying number	ClinicalTrials.gov (NCT05844605)
Date of registration in primary registry	04/05/2023
Secondary identifying numbers	Protocol ID 2020330
Source(s) of monetary or material support	Fundación Joan Ribas Araquistain (reference project 2020.330) Fundaciò La Maratò De TV3 (reference project 201735.10) Fundaciò Bancària La Caixa (reference project LCF/PR/PR16/11110004)
Primary sponsor	Institut Guttmann, Institut Universitari de Neurorehabilitació adscrit a la UAB, Badalona, Spain
Contact for public or scientific queries	Name: [name] Email address: [contact] [contact] Postal address: [name]
Title	Neuromodulation-Induced Prehabilitation to leverage neuroplasticity before surgery for brain tumors: protocol for a single-cohort feasibility trial.
Countries of recruitment	Spain
Health condition(s) or problem(s) studied	Primary brain tumor
Intervention(s)	Neuromodulation, behavioral training, neurosurgery
Key inclusion and exclusion criteria	Inclusion: diagnosis of primary brain tumor requiring neurosurgery Exclusion: contraindications to TMS or MRI
Study type	Single-arm pilot feasibility trial
Date of first enrollment	21 June 2021
Target sample size	20
Recruitment status	Recruiting
Primary outcome(s)	Feasibility
Key secondary outcomes	Changes pre-/post-intervention on clinical, neurophysiology, and neuroimaging outcomes

Study data are collected and managed using REDCap electronic data capture tools hosted at Guttmann Institute (76, 77). To ensure confidentiality, each study participant is identified with an alphanumerical code. Data from neurophysiology and neuroimaging are anonymized and stored on online cloud platforms. Accessibility to data files is granted by the principal investigator only to researchers involved in data management. The hard copy of informed consent forms and other data collected on paper is stored in a locked closet at the Guttmann Institute, accessible only by the principal investigator.

Anonymized data supporting study findings are available from the corresponding author, upon reasonable request. Alternatively, an online data repository named “Joan Ribas Araquistain Dataset on Brain Tumor Prehabilitation” is created and made accessible upon reasonable request to accredited clinicians, researchers, and institutions in the field of neuro-oncology. Furthermore, we sought to establish collaboration agreements with international oncology databases, such as the Georgetown Database of Cancer (G-DOC), REMBRANDT (Repository of Molecular Brain Neoplasia Data), and the Cancer Imaging Archive.

The results of the study will be submitted to a peer-reviewed journal and presented at scientific congresses.

### Statistical analysis

We use R software for statistical analysis and graphics (78). Given the small sample size (20 patients, based on a realistic estimate of the recruitment rate) and the use of ordinal scales, we perform non-parametric statistics. For descriptive reporting of continuous/ordinal variables, median and interquartile range (IQR) are used to indicate measures of central tendency and dispersion, respectively; frequencies are reported by indicating the absolute value, followed by the relative value (percentage) in brackets; in case of binary variables (such as gender), only one of the two variables is reported. For the primary analysis (feasibility), we report descriptively whether we met the criteria for recruitment, retention, and adverse events; adherence to treatment (both neuromodulation and behavioral training) is reported as the median (IQR). An exploratory analysis of effectiveness is conducted by performing a repeated-measure comparison (pre- vs. post-prehabilitation). Together with reporting the estimates of treatment effect, we indicate the actual level of significance (two-sided *p*-value) and 95% confidence interval (79). For quantitative and ordinal variables, we use Wilcoxon signed-rank test. For dichotomous variables, we use McNemar's test. For correlations between quantitative/ordinal variables measured at the same time point, we use Kendall's tau rank correlation coefficient. To explore prediction models, we use simple and multiple linear regression analyses for continuous/ordinal outcomes and simple and multiple logistic regression for binary outcomes. In case of missing data, we perform pairwise deletion. Further explorative analysis may include big data analysis of neuroimaging/neurophysiology data.

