#### Measurement of motor function, independency, and quality of life

Clinical assessments of upper limb motor function include the following measurements:

- Nine-Hole Peg Test (9HPT) evaluates manual dexterity (17, 18). A dedicated platform is placed in front of the patient, with nine pegs inside a container on the side to be evaluated, and nine holes on the other side. The patient is asked to place pegs into the holes and then put them back in the container, as fast as possible; they are allowed to perform a practice trial before the test trial. The therapist has a stopwatch to measure the time to complete the task and instructs the patient in case of errors (more than one peg picked up at the same time, pegs dropped on the table/floor, etc.). Excellent inter-rater and intra-rater reliability (19, 20) and sensitivity to change have been reported for patients with multiple sclerosis and other neurological disorders (20, 21).- Fugl–Meyer upper extremity (FM-UE) evaluates upper limb motor impairment, from reflex activity to voluntary motor control out of synergies (22). There are four separate sections, for the assessment of motor function at the level of the arm, the wrist, the hand, and speed–tremor coordination during a finger-to-nose task. Each item is scored as 0, 1, or 2, with a total score ranging from 0 to 66, with lower scores indicating more severe motor impairment. Excellent intra- and inter-rater reliability has been established (23), together with other psychometric measures related to validity, sensitivity, and responsiveness to change (24–26).- Shoulder abduction finger extension (SAFE) is a quick clinical assessment of upper limb strength, defined as the ability to perform abduction of the shoulder and extension of the index finger; it has potentially high prognostic value for neurological disorders, such as stroke (22). Scoring is usually based on the Medical Research Council scale, ranging from 0 (no visible muscle contraction) to 5 (normal). For the present study, we consider the corresponding items from FM-UE (27).- To quantify the strength of the hand grip, we use an electronic hand dynamometer. According to the standardized setup, patients are holding the dynamometer while sitting, shoulder adducted and neutrally rotated, elbow at 90-degree flexion, and forearm halfway between pronation and supination (28). They are asked to perform a maximal grip strength effort for 3 s, rest for 60 s, and then repeat the measurement two more times; the average of the three trials is used as the most reliable test result (29). Excellent test–retest reliability has been established (30).- Reaction time tasks are useful to measure the efficiency of basic processes for perception and response execution. For the present study, we use the Deary–Liewald reaction time task, a freely available program with established validity and reliability (31). In the simple reaction task paradigm, the patient is facing a blue computer screen with one white window in the center, and the index finger of the hand that is being evaluated over the space bar. The instruction is to click on the space bar as soon as an ‘X' appears on the white window; practice trials are allowed before the test trial, which consists of 20 stimuli with a random interval (1–3 s) in between. In the choice reaction task paradigm, there is a similar setup; this time there are four white windows aligned in the center of the screen, and the patient is holding the fingers over the four corresponding letters of the keyboard. Every stimulus consists of an “X” appearing randomly in one of the four windows; patients are instructed to click the corresponding letter as soon as possible. Practice trials are allowed before the formal test trial. For the present study, we adapted the program of reaction time tasks to evaluate one hand at a time without stringent time constraints.

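### The plan chooses non-parametric methods because of 20 patients and ordinal scales, then assigns linear regression to ordinal outcomes and standard multiple logistic regression to binary ones (minor)

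*Protocol article*

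**What the plan says.** All the relevant statements are in one paragraph, the Statistical analysis section of the protocol article.

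- Reason for the choice of methods: a small sample of 20, "and the use of ordinal scales, we perform non-parametric statistics".
- Pre/post comparison: "For quantitative and ordinal variables, we use Wilcoxon signed-rank test". Correlations use Kendall's tau. Both fit the stated reason.
- Prediction models, introduced with "To explore prediction models": "we use simple and multiple linear regression analyses for continuous/ordinal outcomes and simple and multiple logistic regression for binary outcomes".
- Missing data: "In case of missing data, we perform pairwise deletion". The number of patients in a model can therefore fall below 20.

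The outcomes are described under Measurement of motor function, independency, and quality of life. They include a long sum score, the Fugl-Meyer upper extremity: "Each item is scored as 0, 1, or 2, with a total score ranging from 0 to 66". They also include short or coarse measures: SAFE (taken from Fugl-Meyer items scored 0 to 2), the 12-item hierarchical Brunel balance assessment, NANO and KPS. The section on prehabilitation motor training expects most patients to be fairly young, with few or no motor or cognitive symptoms before surgery.

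**The concern.** The same facts (20 patients, ordinal scales) support rank methods in one sentence and are set aside a few sentences later. Least-squares regression is parametric. At n of 20 or less, its p-values and intervals depend on roughly normal residuals with constant variance. If most patients have few symptoms, many scores may sit at or near the maximum, and those assumptions then become hard to defend.

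The word "multiple" adds a second problem. Two or more predictors in 20 patients or fewer leave little information per coefficient. Apparent fit is then inflated by chance, and some logistic models may have no finite estimate. What is at stake is the credibility of any reported predictor of response, in a field where the article counts seven earlier patients, only one of them treated non-invasively.

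**Working it through.** **Inputs from the article.** n = 20 (Statistical analysis; the registration table agrees). This is a recruitment estimate, so there is no sample-size formula to reproduce. The retention criterion is at least 75%, so the smallest number of completers that still meets it is 0.75 × 20 = 15. That is a floor, not a forecast. Patients are allocated to upper-limb or language training (Figure 1 legend), so some outcomes may exist in fewer than 20.

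**Inputs assumed, because the article does not give them.** Number of predictors k = 1 to 5; predictor type normal or binary; 2 to 10 events.

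**1. The sentences side by side**

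| Task | Method named for ordinal variables | Fits the stated reason? |
|---|---|---|
| Pre/post change | Wilcoxon signed-rank | Yes |
| Correlation | Kendall's tau | Yes |
| Prediction model | Simple or multiple linear regression | No |

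**2. Events per predictor (EPV), logistic regression.** EPV = (size of the smaller outcome class)/k. At n = 20 the smaller class is at most 10.

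| k | 10 events | 5 events |
|---|---|---|
| 2 | 10/2 = 5.0 | 5/2 = 2.5 |
| 3 | 10/3 = 3.3 | 5/3 = 1.7 |
| 5 | 10/5 = 2.0 | 5/5 = 1.0 |

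Any multiple logistic model therefore has an EPV of 5 or less, whatever the event rate.

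**3. Apparent fit with no true association.** For linear regression, E(R²) = k/(n − 1).

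| k | n = 20 | n = 15 |
|---|---|---|
| 1 | 1/19 = 0.05 | 1/14 = 0.07 |
| 2 | 2/19 = 0.11 | 2/14 = 0.14 |
| 3 | 3/19 = 0.16 | 3/14 = 0.21 |
| 5 | 5/19 = 0.26 | 5/14 = 0.36 |

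For logistic regression, the mean apparent AUC was simulated with normal noise predictors, n = 20 and 500 runs per cell. The true value is 0.50.

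| k | 10 events | 5 events | 3 events |
|---|---|---|---|
| 1 | 0.60 | 0.62 | 0.65 |
| 2 | 0.66 | 0.69 | 0.72 |
| 3 | 0.71 | 0.74 | 0.79 |
| 5 | 0.79 | 0.82 | 0.89 |

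**4. Separation.** This is the share of simulated datasets in which a linear-programming check shows that no finite maximum-likelihood estimate exists. Case: 3 noise predictors, n = 20, about 20% events.

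| Assumption | Share |
|---|---|
| All normal, exactly 4 events | about 2% |
| One binary (50%), exactly 4 events | about 13% |
| Two binary (50%), exactly 4 events | about 24% |
| Two binary, event count random | about 37% |
| Two binary (30% prevalence), exactly 4 events | about 46% |

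The result depends on the inputs. With two normal predictors and 3 or more events in 20, separation occurs in about 1% of datasets or fewer. With fewer patients it rises: for 3 normal predictors and 3 events it goes from 6% at n = 20 to 11% at n = 15.

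**The case against.** **Linear regression of sum scores is common practice.** This stands in part. For a 0 to 66 total that spreads well, the objection is weak. It regains force if scores cluster at the ceiling, which is an inference from the description of the patients and not a figure in the article. For short or coarse scales the objection stays strong. The article does not say which scales will be modelled.

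**Number of predictors, penalisation and validation are usually left to a fuller document.** This stands. The lack of a limit on predictors in a condensed article is not a finding by itself. The point rests on what the article does fix: linear regression for ordinal outcomes, and multiple logistic regression at this size. The EPV bound needs only "multiple" to mean two or more.

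**The models are already called exploratory.** This stands and lowers the severity. The primary analysis is a descriptive report of feasibility and is unaffected.

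**Proportional-odds models are also fragile at n = 20.** This is true. They need one intercept per cut-point, and their estimates will be imprecise. The gain is a model that suits the outcome type, not precision.

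**A reader might also fault McNemar's test.** The article does not support this. It says "For dichotomous variables, we use McNemar's test" and names no version. Only the uncorrected chi-square misleads: p = 0.046 for 4 versus 0 discordant pairs and 0.025 for 5 versus 0. The exact values are 2 × 0.5⁴ = 0.125 and 2 × 0.5⁵ = 0.0625. The continuity-corrected values are 0.134 and 0.074, slightly more conservative than exact.

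**Conclusion.** The inconsistency is real and lies within one paragraph. Its stated reason for non-parametric methods applies equally to the prediction models, yet parametric linear regression is named for ordinal outcomes. Multiple logistic regression in at most 20 patients has an EPV of 5 or less in every case. Unrelated predictors would show an expected R-squared of 0.11 to 0.26 (k = 2 to 5, n = 20).

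A reader might infer that the logistic models will usually fail to converge, or that the analysis will rest on about 15 patients. Neither is supported. Separation runs from about 2% to 37% or more in the case examined, depending on predictor type and event count, and is rare with two normal predictors. Fifteen is only the retention floor. One-predictor models are estimable: with normal predictors and 2 to 10 events at n = 20, separation occurs in 0 to 1% of datasets, and their optimism is modest.

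Severity: minor, because the models are exploratory and the primary feasibility outcome does not depend on them.

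**What to change.** In the Statistical analysis section:

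1. For ordinal outcomes, replace linear regression with proportional-odds (ordinal logistic) regression, collapsing sparse levels where needed. Keep linear regression for continuous outcomes.
2. For binary outcomes, replace standard logistic regression with Firth-penalised logistic regression, which gives finite estimates under separation.
3. Restrict each exploratory model to one predictor, plus the baseline value where the outcome has one. Some surgical outcomes, such as the amount of tumor removed, have none.

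The cost is a change of wording, since these models can be fitted in R, which the plan already uses. The downsides are fewer exploratory models and proportional-odds estimates that remain imprecise at this size. The restriction reduces optimism but does not remove it. With one noise predictor at n = 20, the expected R-squared is still 0.05 and the apparent AUC 0.60 to 0.65 (10 to 3 events). Where the baseline value is added, the k = 2 figures above apply.
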